### Statistical analyses

#### Analysis populations and general principles.

All randomized participants who receive at least one treatment session will be included in the primary analysis set. Safety analyses will include all participants who receive at least one session of active or sham stimulation. Baseline characteristics will be summarized descriptively by treatment group. Continuous variables will be presented as mean and standard deviation or median and interquartile range, as appropriate, and categorical variables will be presented as frequencies and percentages.

As this is a pilot trial, the statistical analyses will focus primarily on estimation rather than definitive hypothesis testing. Effect estimates and corresponding 95% confidence intervals will be reported where appropriate, and P values will be interpreted cautiously as supportive rather than confirmatory. No formal adjustment for multiplicity is planned, given the exploratory nature of the trial.

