## Methods

### Study design and setting

This investigator-initiated, single-center pilot trial is designed to evaluate the feasibility, safety and preliminary clinical efficacy of rs-fcMRI-guided rTMS in adolescents with MDD. Participants will be randomly assigned to one of three parallel arms: conventional left dorsolateral prefrontal cortex (DLPFC)-targeted rTMS, rs-fcMRI-guided rTMS targeting an individualized DLPFC site defined by DLPFC-sgACC functional connectivity, or sham rTMS.

The study adopts a randomized, double-blind, three-arm, sham-controlled, parallel-group pilot design and will be conducted at the First Affiliated Hospital of Chongqing Medical University (Chongqing, China) from September 2025 to September 2027. A total of 45 adolescents will be enrolled, with 15 participants allocated to each group in a 1:1:1 ratio. Participant recruitment commenced in September 2025 and is expected to be completed by December 2026. Recruitment will be monitored throughout the study to assess enrolment feasibility and ensure timely participant accrual. At the time of manuscript submission, the study is ongoing, and no study results have been generated. Data collection is expected to be completed by June 2027, and study results are anticipated to be available by September 2027.

The study protocol was approved by the Ethics Committee of the First Affiliated Hospital of Chongqing Medical University (Ethical Approval No. 2025-533-01) and registered at ClinicalTrials.gov (NCT07185438).

This pilot trial consists of a 7-day screening period, a 4-week intervention phase, and follow-up assessments up to 6 months. After eligibility has been confirmed, participants and their legal guardians will provide written informed consent, and participants will undergo baseline assessments, including MRI. Participants will then be randomly assigned to one of three groups to receive a 4-week course of active or sham rTMS. Follow-up assessments will be performed at weeks 8, 16, and 24 to evaluate clinical outcomes and safety over time. Cognitive and multimodal measures, including EEG, fNIRS, eye-tracking measures, facial expression features, and acoustic features, will also be collected at baseline, at the end of treatment, and during follow-up as exploratory measures.

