### Sample size

As a pilot trial, this study is not designed or powered to test definitive treatment efficacy. A total of 45 MDD adolescents will be enrolled, with 15 participants allocated to each of the three study arms. The sample size was determined pragmatically on the basis of feasibility, anticipated clinical capacity, and available study resources. This sample size is intended to provide estimates of recruitment feasibility, intervention adherence, retention, safety, and preliminary clinical efficacy signals, as well as variability parameters needed to refine the protocol and inform the sample size calculation for a future fully powered randomized controlled trial.

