### Stimulation targets

Participants in the rs-fcMRI-guided rTMS group will receive stimulation at an individualized left DLPFC target identified under MRI guidance as the voxel showing the strongest negative resting-state functional connectivity with the sgACC. Participants in the conventional left DLPFC-targeted rTMS group will receive MRI-guided stimulation at the predefined left DLPFC target. Participants in the sham rTMS group will receive sham stimulation matched in appearance, sound, and procedural experience to active treatment in order to help maintain participant blinding.

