## Outcomes

### Primary outcomes

The primary outcomes of this pilot trial are feasibility, safety, and preliminary clinical efficacy.

Feasibility will be evaluated using three indicators: recruitment feasibility, intervention adherence, and retention at the 6-month follow-up. Recruitment feasibility will be defined as the number of participants successfully enrolled during the 2-year recruitment period. Intervention adherence will be defined as the proportion of participants who complete all 20 planned treatment sessions. Retention will be defined as the proportion of enrolled participants who complete the 6-month follow-up assessment.

Safety will be evaluated by recording the incidence of adverse events and serious adverse events throughout the treatment and follow-up periods. The type, severity, outcome, and relationship of each adverse event to the intervention will be documented.

Preliminary clinical efficacy will be evaluated using the CDRS-R. CDRS-R total score will be assessed at baseline, at the end of treatment (week 4), and at follow-up weeks 8, 16, and 24. Response will be defined as a reduction of at least 50% in the CDRS-R total score from baseline, and remission will be defined as a CDRS-R total score of 28 or lower [28]. Response and remission will be determined at post-baseline assessments, using the baseline CDRS-R total score as the reference.

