## Discussion

This study is a randomized, double-blind, three-arm, sham-controlled, parallel-group pilot trial designed to evaluate the feasibility, safety, and preliminary clinical efficacy of rs-fcMRI-guided rTMS targeting a circuit-informed DLPFC-sgACC axis in adolescents with MDD [33,34]. By directly comparing rs-fcMRI-guided individualized targeting with conventional left DLPFC stimulation and sham stimulation, the trial aims to clarify whether this imaging-guided neuromodulation approach can be delivered reliably in adolescents while also generating early clinical signals.

Although rTMS is an established treatment for adult depression and is generally associated with good tolerability and mostly mild, transient adverse effects [35], evidence in adolescent MDD remains limited and inconsistent. Existing studies differ substantially in design, stimulation targets, treatment parameters, and participant characteristics, which may partly explain the heterogeneity of reported findings. Moreover, the practical feasibility of delivering repeated rTMS sessions together with MRI and multimodal assessments in adolescents has not been adequately characterized. These uncertainties support the need for a pilot trial that addresses both clinical promise and real-world implementation.

The rationale for rs-fcMRI-guided targeting is grounded in adult neuroimaging evidence suggesting that antidepressant response to rTMS may be greater when stimulation is delivered to left DLPFC sites showing the strongest negative functional connectivity with the sgACC, a key node within depression-related neural circuits [36]. Compared with conventional targeting methods, this approach may allow more precise modulation of fronto-limbic networks involved in mood regulation. Accordingly, the present study will explore whether individualized rs-fcMRI-guided stimulation of the DLPFC-sgACC circuit is associated with more favorable preliminary clinical signals than standard left DLPFC stimulation in adolescents with MDD. It will also examine whether symptom improvement is accompanied by modulation of DLPFC-sgACC connectivity and broader changes in depression-relevant networks.

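### The primary analysis set leaves out randomised participants who never start, its denominator conflicts with the outcome definitions, and no indicator counts whether an individual target was obtained

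*Protocol article*

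**What the plan says.** Under Analysis populations and general principles, the article states: "All randomized participants who receive at least one treatment session will be included in the primary analysis set". The safety set in the same paragraph is everyone who receives at least one active or sham session, so the two sets have the same members and no all-randomised set is defined.

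Under Primary outcomes: "Feasibility will be evaluated using three indicators: recruitment feasibility, intervention adherence, and retention at the 6-month follow-up". The denominators there are worded differently. For retention: "Retention will be defined as the proportion of enrolled participants who complete the 6-month follow-up assessment". For adherence: "Intervention adherence will be defined as the proportion of participants who complete all 20 planned treatment sessions". The section on analysis of primary outcomes names a set for safety only.

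Under Stimulation targets, the guided arm is treated at an "individualized left DLPFC target identified under MRI guidance as the voxel showing the strongest negative resting-state functional connectivity with the sgACC". The conventional arm is treated, also under MRI guidance, at a predefined site. The Discussion says the trial is to clarify "whether this imaging-guided neuromodulation approach can be delivered reliably in adolescents".

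Three further statements bear on timing and recording. Study design and setting places baseline MRI before randomisation in all arms. Randomization has the envelope opened immediately before the first session. The study-flow paragraph requires counts of participants randomised and treated, with reasons for exclusion or discontinuation.

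**The concern.** Adherence and retention are primary outcomes of a feasibility trial, so their denominators are part of the result. A participant who is allocated but never treated is a failure of delivery. Under the stated analysis set that participant is removed from the denominator instead of being counted as a non-completer.

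The loss need not be equal across arms. Before treatment in the guided arm, the resting-state data must yield an individual voxel; the other two arms do not depend on that step. If the target is computed after allocation, a failure there could remove participants from one arm only.

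Separately, obtaining an individual target is the step that distinguishes the guided approach, and the Discussion makes reliable delivery an aim. Yet no indicator under Primary outcomes, in Table 1 or in the primary analysis section counts it, and it is not among the process indicators exemplified in the Discussion. The Discussion also says the feasibility results will help decide whether the protocol needs modification before a larger trial, so a favourable adherence figure that hides failures at this step would mislead that decision.

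**Working it through.** **The plan's own figure.** The article gives "A total of 45 adolescents will be enrolled, with 15 participants allocated to each group in a 1:1:1 ratio": 3 × 15 = 45, and with the stated block size of 9, 45/9 = 5 complete blocks. Both agree. On the basis of the size, it says: "The sample size was determined pragmatically on the basis of feasibility, anticipated clinical capacity, and available study resources". There is no power or precision calculation to reproduce.

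**Inputs.** From the document: n = 15 randomised per arm. Assumed, because the document gives no rates: k = 0 to 3 never-starters in the arm, c = 12 completers, and a target-failure probability q of 2% to 20%.

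**Shift in adherence.** With all randomised as denominator the rate is c/n. With starters only it is c/(n − k). The difference is c/(n − k) − c/n = ck/[n(n − k)]. Intervals are exact (Clopper-Pearson) 95%.

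| Never-starters k | All randomised | Starters only | Shift (points) |
|---|---|---|---|
| 0 | 12/15 = 80.0% (51.9 to 95.7) | 12/15 = 80.0% (51.9 to 95.7) | 0 |
| 1 | 12/15 = 80.0% | 12/14 = 85.7% (57.2 to 98.2) | 12/210 = 5.7 |
| 2 | 12/15 = 80.0% | 12/13 = 92.3% (64.0 to 99.8) | 24/195 = 12.3 |
| 3 | 12/15 = 80.0% | 12/12 = 100% (73.5 to 100) | 36/180 = 20.0 |

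The same algebra applies to a response or remission rate, with c the number of responders or remitters, if never-starters are counted as not having responded or remitted.

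**How likely is at least one target failure in an arm of 15?** 1 − (1 − q)^15 gives 26% at q = 2%, 54% at 5%, 79% at 10% and 97% at 20%. These are chances of a failure, not of a never-starter. A failure becomes a never-starter only if the target is computed after allocation and no session follows.

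**The two possible workflows.** The article does not say when targets are computed.

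- *After allocation:* a failure can fall in the guided arm only and can leave the primary analysis set. An all-randomised set would keep it.
- *Before allocation:* a failure, if it stops the participant going forward, is lost before randomisation from all arms alike. An all-randomised set does not recover it. Only a count over scanned participants does.

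In both workflows target success is absent from the listed outcomes.

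**Precision of a target-success proportion.** Baseline MRI is done in every arm, so the proportion can be estimated over all scanned participants, not only the guided arm. As an illustration at an assumed 93% success, the Wilson 95% interval is 82% to 98% for 42/45 and 70% to 99% for 14/15. The widths are about 16 and 29 points.

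**The case against.** A reader might infer that feasibility in the guided arm *is* overstated, through a loss that occurs in that arm alone. The documents do not support this as a fact, for several reasons, all of which stand.

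- **Timing.** MRI precedes randomisation in everyone and the envelope is opened immediately before the first session. The interval in which an allocated participant could fail to start is short unless the target is computed after allocation, and the article does not say that it is.
- **Retention.** Its own definition already uses enrolled participants. If that specific definition governs over the general sentence, retention is not inflated.
- **Adherence.** Its denominator is ambiguous. Inflation follows only if the restricted set is applied.
- **Contrast between arms.** The conventional arm is also MRI-guided, and navigation rests on each participant's MRI. Only a failure confined to the resting-state data is specific to the guided arm.
- **Recording.** The flow record would show randomised but untreated participants with reasons, so such losses would not be invisible. The further process indicators are given only as examples, so that list is open.
- **Efficacy.** Between-group comparisons are optional and exploratory, so it would be too strong to say that a randomised test is invalidated.

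Detailed scan quality rules may also sit in a fuller protocol that is not shown, and their absence here is not a fault. What remains does not depend on them. The article does fix a restricted primary set, it does word the outcome denominators differently, and its closed list of three feasibility indicators omits the step that its own Discussion aim depends on. A flow count with reasons is not a prespecified proportion with a denominator and an interval.

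**Conclusion.** The point holds in conditional form. Two things are established from the text: the analysis set and the outcome denominators are not reconciled, and no named indicator measures target generation. That adherence and efficacy rates *can* be biased upward follows if the restricted set is applied. That the bias can differ by arm needs the further condition that targets are computed after allocation.

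The size is unknown. Under the assumed 12 completers of 15, it runs from zero, if nobody is lost between allocation and the first session, to 20.0 points with three never-starters. With arms of 15, even one never-starter moves the figure by 5.7 points. This is a worthwhile and nearly costless improvement to a primary feasibility outcome, not a demonstrated error in a result.

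**What to change.** 1. **Analysis set.** State that adherence, retention and efficacy are analysed in all randomised participants by assigned arm, and keep the one-session condition for the safety set only. Word the adherence and retention definitions to match, so that Primary outcomes and Analysis populations agree. State how a never-starter without a week-4 CDRS-R score enters the response and remission rates.
2. **Target generation.** Run scan quality control and target generation for every participant before the envelope is opened, and state whether a participant without a target is still randomised.
3. **Indicator.** Add as a feasibility measure the proportion of scanned participants with both a usable rs-fcMRI scan and an individual target, with a 95% Wilson interval. The denominator is everyone scanned, including anyone lost before randomisation.

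**Cost.** Changes of wording, and the target pipeline run on about 2 × 15 = 30 further scans (conventional and sham arms) that are acquired anyway. Recruitment has begun, so scans already taken would be processed retrospectively and the change made by the amendment route the article describes. The article reports that no results have been generated, so the change can still be made without reference to outcomes. The downside is that adherence may look slightly lower.

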#### Analysis of primary outcomes.

Primary outcomes will be analyzed descriptively in accordance with the pilot nature of the trial. Feasibility outcomes will include recruitment feasibility, intervention adherence, and retention at the 6-month follow-up. Recruitment feasibility will be summarized as the number of participants enrolled during the recruitment period. Intervention adherence and retention will be summarized as frequencies and proportions, with corresponding 95% confidence intervals calculated where appropriate.

Safety outcomes will be analyzed in the safety analysis set, defined as all participants who receive at least one session of active or sham stimulation. The incidence of adverse events and serious adverse events will be summarized by treatment group as the number and proportion of participants experiencing at least one event. Event counts, severity, outcomes, and relationship to the intervention will also be summarized descriptively.

Preliminary clinical efficacy will be evaluated in terms of response and remission based on CDRS-R total scores. Response and remission rates will be summarized descriptively by treatment group at the end of treatment and at each follow-up assessment, with 95% confidence intervals. Exploratory between-group comparisons may be conducted using logistic regression models at individual post-baseline time points or generalized estimating equations for repeated binary outcomes across follow-up, as appropriate. Effect estimates will be presented as odds ratios with 95% confidence intervals.

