### Concomitant medication management

Participants must be receiving a stable pharmacological treatment regimen, defined as no changes for at least 4 weeks before enrolment, and are required to maintain this regimen throughout the trial unless modification is clinically indicated. Concomitant medications and any treatment adjustments will be systematically documented at each study visit to minimize potential confounding arising from medication changes.

For analyses of preliminary clinical efficacy, baseline medication-related factors will be considered as covariates in the primary outcome model to support estimation of treatment effects under relatively stable pharmacological conditions. Pre-specified sensitivity analyses will also be conducted to examine the robustness of the findings under alternative medication scenarios and protocol deviations. Collectively, these procedures are intended to facilitate interpretation of treatment effects within a relatively stable medication context.

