#### Analysis of secondary outcomes.

Secondary outcomes, including BDI-II, HAMA, SCARED, C-SSRS, PSQI, PedsQL 4.0, CGI-S, CGI-I, and RRS, will be analyzed according to outcome type. Repeated continuous outcomes will primarily be analyzed using linear mixed-effects models, where appropriate, with treatment group, time, and treatment-by-time interaction included as fixed effects and the corresponding baseline value included as a covariate. CGI-I will be analyzed as a post-baseline global improvement rating. Ordinal or categorical outcomes will be analyzed using appropriate generalized linear models, generalized estimating equations, ordinal regression models, or non-parametric methods, depending on the distribution and scale properties of the data. Results will be summarized at each prespecified assessment time point together with effect estimates and 95% confidence intervals where appropriate.

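### The CDRS-R total score is assigned to no model, so the protocol commits to no mean difference or post-treatment SD for its only primary efficacy scale

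*Protocol article*

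**What the plan says.** All of this is in the protocol article.

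- **Primary outcomes** makes CDRS-R the sole efficacy scale among the primary outcomes: "Preliminary clinical efficacy will be evaluated using the CDRS-R". The schedule is: "CDRS-R total score will be assessed at baseline, at the end of treatment (week 4), and at follow-up weeks 8, 16, and 24". The total is then cut in two ways. For response: "Response will be defined as a reduction of at least 50% in the CDRS-R total score from baseline". Remission is a total of 28 or lower.
- **Table 1** has one CDRS-R row, and it lists only response or remission at week 4.
- **Analysis of primary outcomes** opens by calling the analysis descriptive, then fixes the form of the efficacy analysis: "Preliminary clinical efficacy will be evaluated in terms of response and remission based on CDRS-R total scores". Rates by arm and visit with 95% confidence intervals come first. Logistic or GEE comparisons may follow, and the article fixes how these are reported: "Effect estimates will be presented as odds ratios with 95% confidence intervals". No other effect measure is named for CDRS-R.
- The section on **secondary outcomes** in the statistical analyses names its scales: "Secondary outcomes, including BDI-II, HAMA, SCARED, C-SSRS, PSQI, PedsQL 4.0, CGI-S, CGI-I, and RRS, will be analyzed according to outcome type". For scales in that list that are continuous and repeated, the plan is a linear mixed model with arm, visit, their interaction and the baseline value. CDRS-R is not listed.
- **Missing data and sensitivity analyses** has a general sentence making mixed models the main approach for repeated continuous outcomes. It does not name CDRS-R.
- **Concomitant medication management**: "baseline medication-related factors will be considered as covariates in the primary outcome model".
- **Sample size** says that the 45 participants should yield, among other things, "variability parameters needed to refine the protocol and inform the sample size calculation for a future fully powered randomized controlled trial". **Analysis populations and general principles** says the emphasis is on estimation.

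**The concern.** The pilot exists to estimate quantities and to equip a later trial. A later trial that uses the CDRS-R total would need the SD of the post-treatment or change score, and would want a mean difference with its interval. The planned CDRS-R output supplies neither. The secondary scales, and even the continuous exploratory measures, are given models of the score itself, so the primary efficacy scale has the least informative analysis of the three tiers.

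Two further problems follow. Cutting a score at a threshold wastes information that 15 participants per arm can ill afford. And the medication section refers to a primary outcome model that the primary-outcome analysis, described there as descriptive, never defines.

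**Working it through.** **1. The plan's own figure.** 3 arms × 15 = 45, as stated. The size is pragmatic. No alpha, power, effect size, SD or response rate is given, so there is no power calculation to reproduce. Every response rate below is an assumption.

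**2. Where each CDRS-R quantity is planned.**

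| Quantity | Committed to? | Section |
|---|---|---|
| Baseline mean and SD | Likely | General principles (summary of continuous variables) |
| Response and remission rates with 95% CI | Yes | Analysis of primary outcomes |
| Odds ratios between arms | Optional | Analysis of primary outcomes |
| Mean difference in total score | No | None names it |
| SD of post-treatment or change score | No | None names it |

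**3. Information lost by dichotomising.** For a normal score cut so that a proportion p respond, the asymptotic efficiency relative to the score itself is φ(z_p)² / [p(1 − p)]. This is an approximation for response, which is a percentage change, and applies more directly to remission, which is a cut of the total.

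| Assumed p | φ(z_p) | Efficiency | Loss | Effective n of 15 |
|---|---|---|---|---|
| 50% | 0.399 | 0.159/0.25 = 0.637 | 36% | 9.5 |
| 30% | 0.348 | 0.121/0.21 = 0.576 | 42% | 8.6 |
| 20% | 0.280 | 0.0784/0.16 = 0.490 | 51% | 7.3 |
| 10% | 0.1755 | 0.0308/0.09 = 0.342 | 66% | 5.1 |

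**4. Precision of the odds ratio.** Take 3/15 against 6/15 responders as an example. OR = (6/9)/(3/12) = 2.67. The SE of log OR = √(1/3 + 1/12 + 1/6 + 1/9) = 0.833. The 95% CI is 2.67 × exp(±1.96 × 0.833) = 0.52 to 13.7.

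**5. Estimability.** An odds ratio involving an arm with 0/15 or 15/15 events has no finite maximum-likelihood estimate. The probability that at least one arm is in that state is 1 − Π[1 − (1 − p)¹⁵ − p¹⁵].
- Rates 10/20/30%: the zero-event probabilities are 0.206, 0.035 and 0.005, so 1 − 0.794 × 0.965 × 0.995 = 24%.
- Rates 15/25/35%: 10%.
- Rates 20/35/50%: 4%.

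**6. What the score would give instead.** With 15 complete per arm, the 95% half-width of an unadjusted mean difference is t(0.975, 28) × √(2/15) = 2.048 × 0.365 = 0.75 SD. Baseline adjustment would narrow this to the extent that baseline predicts outcome. A pooled SD on 45 − 3 = 42 degrees of freedom has a 95% interval of 0.82 to 1.27 times its estimate. That is imprecise, but it is the kind of variability parameter that the Sample size section promises.

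**The case against.** The strongest reply is that the plan already covers this. The missing-data section makes mixed models the main approach for repeated continuous outcomes without restricting this to secondary scales, and a CDRS-R total taken at five visits fits that description. A separate statistical analysis plan exists and is not shown. The totals are collected, so an SD can be computed at any time. The trial is an unpowered pilot, and BDI-II, another depression measure, already has a mixed model.

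Much of this stands as a limit on severity. It does not remove the point. The general sentence concerns missing data and does not name CDRS-R, while the section that does deal with CDRS-R makes it binary, and Table 1 agrees. The finding rests on what the article fixes, not on details left to another document.

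A reader might infer several stronger things that the document does not support:

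- **That odds ratios are the only CDRS-R output, or that there is no CDRS-R effect or SD at all.** Rates with intervals are the main output, odds ratios are optional, and a baseline SD is likely.
- **That the proportions could have infinite intervals.** An interval for a proportion is always finite. Only an odds ratio can diverge.
- **That medication covariates would sharply raise the share of non-estimable treatment odds ratios.** Simulating three assumed binary indicators (prevalence 25, 20 and 15%) separates some coefficient in about half of trials at 10/20/30%, but mostly a nuisance one. A treatment odds ratio is non-estimable in about 25% of trials, against 24% without covariates. At 15/25/35% it is about 10% either way.
- **That GEE contradicts the missing-at-random assumption.** The article attaches that assumption to mixed models for continuous outcomes, and lists multiple imputation as a sensitivity analysis.

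**Conclusion.** The point holds. As written, the protocol names no model for the CDRS-R total and commits to no mean difference and no post-treatment or change SD for its only primary efficacy scale. That fits poorly with its stated aims of estimation and of informing the next sample size.

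The loss from using only the binary forms is about a third to two thirds of the information, close to half at a 20 to 25% response rate. This assumes an approximately normal score and response rates that the document does not give. Non-estimable odds ratios are a real risk only if response is low in some arm.

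Severity is moderate. The damage is to estimation and planning, and no confirmatory conclusion depends on it.

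**What to change.** 1. In Analysis of primary outcomes, state that the CDRS-R total will be analysed with the mixed model already specified for the secondary scales: arm, visit, arm-by-visit and baseline CDRS-R, using weeks 4 to 24. Report adjusted mean differences with 95% confidence intervals and the residual SD. Also report the observed SD of the score and of its change at each visit.
2. Keep response and remission rates with their intervals, as planned.
3. Reconcile the primary outcome model in Concomitant medication management with the descriptive analysis of primary outcomes. One way is to say that the CDRS-R mixed model is the model meant, with baseline CDRS-R in it, and to name any medication factors that enter.

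The choice of interval method for the proportions, or of penalised likelihood for any odds ratio, can be left to the analysis plan.

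The cost is a few sentences, one more model and one more reported estimate. No new data, visits or participants are needed.
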